### Recruitment {15}

We will assess the eligibility of all patients with SLAC/SNAC pattern wrist OA referred to the study hospitals. These participants will be referred to a RI and screened according to the inclusion and exclusion criteria. We estimate that the recruitment will be completed at the end of 2028.

## Assignment of interventions: allocation

### Sequence generation {16a}

A randomization sequence will be generated using an internet-based program (sealedenvelope.com). Patients will be allocated to one of the two treatment groups in a 1:1 ratio using permuted block randomization with variable block size.

### Concealment mechanism {16b}

The randomization will be performed by the research nurse by opening a sequentially numbered sealed opaque envelope after the surgeon has performed the wrist arthroscopy and confirmed the eligibility of the patient. As the envelopes will be kept in a secure, lockable cabinet that is only accessible by the study nurse located in the Helsinki University Hospital, an operating room nurse at each center will telephone the study nurse to receive and pass the knowledge of the allocation to the surgeon.

### Implementation {16c}

The RI, who is not involved in performing procedures, will enroll patients according to the inclusion and exclusion criteria. The interventions will be performed according to the randomization after the study surgeon has confirmed the eligibility by wrist arthroscopy. Randomization will be performed with the sealed opaque envelope method described above. The randomization sequence will be generated by an independent hand surgeon ([name].) familiar with clinical trial conduct and random sequence generation. [name] is not involved in the execution of the trial.

## Assignment of interventions: blinding

### Who will be blinded {17a}

The trial is patient- and outcome assessor (RI) -blinded. The patient will be blinded to the study intervention throughout the surgery by use of noise-canceling headphones. Moreover, patients will not have visual contact to the operation field or the surgeon performing the intervention. Operating room staff will not discuss the surgical method or disclose it to other hospital staff. No records revealing allocation will be accessible to the study patients.

The RI involved in patient enrolment and performing follow-up examinations will not participate in surgery and will not be able to access patient records containing knowledge of the treatment allocation. Follow-up CBCTs will be reviewed by the surgeon responsible for the intervention and concealed from the patient and RIs. If no (adverse) events compromising the standardized postoperative rehabilitation program are present in radiological evaluation during follow-up, the surgeon will give permission to continue the rehabilitation according to the study protocol.

The primary endpoint is PRWE score at 12 months post-intervention. This will also be the timepoint for unblinding.

### Procedure for unblinding if needed {17b}

In any case of a clinical situation that necessitates the knowledge of the trial group of the participant, patients can be unblinded (e.g., adverse event necessitating reoperation). However, whenever possible, the steering committee will discuss the clinical scenario and decide whether unblinding is necessary before it is performed. Each unblinding that occurs before assessment of primary endpoint will be reported.

## Data collection and management

### Plans for assessment and collection of outcomes {18a}

The RIs will collect all the baseline and follow-up data used for outcome reporting. All RIs are consultant level hand surgeons and will receive training in clinical measurements to improve inter-rater validity. A training log will be used to document all training completed by trial staff members. Moreover, each study center will receive an “investigator file” that contains all trial-related documentation and information to improve data collection.

Perioperative measures will be collected by the surgical team and include arthroscopic findings, type and number of cannulated screws, operation time (arthroscopy and total operative time), and time in the operating theater.

Postoperative outcome measures are discussed in detail in the “Outcomes {12}” section. The RIs will complete all clinical evaluations during follow-up and oversee the completeness of all questionnaire forms with a visual check of the responses. In case of incomplete questionnaires, RIs or SNs will inquire for missing data when possible.

### Plans to promote participant retention and complete follow-up {18b}

Participants may request unblinding at any point of the trial. However, to minimize unblinding before primary endpoint, the following will be addressed prior to trial enrolment to ensure that potential participants:Are willing to receive either of the interventionsAre willing to remain with their allocation for 12 months

Unblinding prior to the 12 months does not affect the follow-up protocol or analyses.

### Data management {19}

A database including patients’ identification information and consent forms will include a unique identification code for each participant. A separate database where the participants are coded with the identification code will include the baseline and outcome data.

All RIs and SNs will be trained for trial electronic database use. When the questionnaire forms are received, the RI or SN will inspect the responses and inquire missing data when possible. The SN performing data entry will be blinded to group allocation. The forms will be stored into a password-protected electronic database on a hospital-provided server by means of double data entry to minimize typing errors. Patient records will be reviewed when collecting missing data or interpreting inconsistent or implausible data.

### Confidentiality {27}

All personal information about potential and enrolled participants are protected according to EU General Data Protection Regulation (GDPR). Case report forms (CRF) and all collected data from each trial center will be de-identified before creating a complete data set used for statistical analysis. No individual patient can be identified from the publication of trial results.

The full participant data will be stored for 12 months from the final conclusion of the study (after the 10-year follow-up visit). RIs are responsible of maintaining and ultimately destroying participant and processed data according to GDPR. Public access to the final trial dataset will be available on request from the principal investigator for research purposes based on steering committee assessment.

### Plans for collection, laboratory evaluation, and storage of biological specimens for genetic or molecular analysis in this trial/future use {33}

This trial does not involve collecting biological specimens for storage.

## Statistical methods

### Statistical methods for primary and secondary outcomes {20a}

Statistical analysis will be performed with both per-protocol and intention-to-treat (ITT) methods, the latter being the primary analysis. Descriptive statistics will be presented as mean (standard deviation) or median (interquartile range) for continuous variables and count (percent) for categorical variables.

For the continuous outcomes, we will compare the groups using a mixed model for repeated measurements (MMRM) entering group, group*time interaction as fixed factors, study site as a random factor, and baseline value as a covariate to the model. Marginal effects with 95% confidence intervals from the model will be reported as treatment effects. For the global improvement, we will use ordinal logistic model.

Statistical significance is set at 0.05. As comparisons of secondary outcomes are considered hypothesis generating, we will not adjust for multiple comparisons.

A statistical software program will be used for analyzing entered data. Blinded data interpretation will be used to reduce interpretation bias; therefore, the biostatistician will be unaware of the group assignments when performing the analyses.

The criterion for statistical significance will be set at *p* = 0.025 (one-sided) or *p* = 0.05 (two-sided). All *p*-values will be reported to three decimal places, with those less than 0.001 reported as *p* < 0.001.

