### Outcomes {12}

The primary endpoint of the study is PRWE at 1 year after the procedure. The secondary outcomes are Quick-Disabilities of Arm, Shoulder, and Hand (Q-DASH), pain on visual analog scale (VAS, 0 = no pain, 10 = worst imaginable pain), EQ-5D-5L, grip strength, wrist active ROM, global improvement, AEs, and radiologic evaluation (progress of arthritic changes, time to fusion in FCA participants) at the 1-year follow-up. Also, long term follow-ups (5 and 10 years) will be conducted.

The baseline data include patient age, gender, hand dominance, affected limb, duration of symptoms, smoking, education, type of work (desk-based to heavy manual), previous injuries, and surgery of the affected limb. Radiological baseline assessment includes wrist OA classification (SLAC/SNAC 0-IV), location of scaphoid non-union (distal, waist, proximal pole), ulnar variance, scapho-lunate- and scapho-capitate angle. Baseline clinical outcomes that will be assessed include ROM, and grip and key-pinch strength measurements.

The outcome variables and participant timeline are presented in Table 4.

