### Participant timeline

Follow-up will take place at 3 and 6 weeks, at 3, 6, and 12 months, and at 5 and 10 years post-treatment. The trial schedule of enrollment, interventions, assessments, and data collection are presented in Table 4.

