### Sample size {14}

The primary outcome measure is PRWE and the primary hypothesis of our trial is that PRC is non-inferior to FCA in the treatment of SLAC/SNAC OA I-II measured with PRWE total score. The non-inferiority margin is set at 11.5 points using the PRWE minimally clinically important difference [31]. To exclude the non-inferiority margin, the trial will require 37 patients in each group to observe MCID (non-inferiority margin 11.5, SD 14) in PRWE scores between the trial groups with a power of 90% and using a one-sided type I error rate of 2.5%. We will recruit 84 patients to account for 10% loss during follow-up.

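### The MMRM as listed adjusts the 12-month PRWE contrast with one baseline slope pooled over all modelled visits; a baseline-by-visit term would be a small, nearly free improvement

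*Protocol article*

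**What the plan says.** Section {20a} of the Protocol article analyses continuous outcomes with a mixed model for repeated measurements, "entering group, group*time interaction as fixed factors, study site as a random factor, and baseline value as a covariate to the model". It adds: "Marginal effects with 95% confidence intervals from the model will be reported as treatment effects". No interaction of baseline with time is listed. The same sentence names no main effect of time, no covariance structure and no visit for the marginal effect.

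The primary endpoint is tied to one visit. Section {12} says "The primary endpoint of the study is PRWE at 1 year after the procedure", and section {17a} agrees: "The primary endpoint is PRWE score at 12 months post-intervention". The Participant timeline states: "Follow-up will take place at 3 and 6 weeks, at 3, 6, and 12 months, and at 5 and 10 years post-treatment". Which of these visits collect PRWE is set out in Table 4, which is not reproduced in the text available. The sample size section {14} uses "non-inferiority margin 11.5, SD 14" and concludes that "the trial will require 37 patients in each group". Section {16a} describes permuted blocks and mentions no stratification.

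**The concern.** A model with a group-by-time term estimates a separate group difference at each visit. If baseline enters only as a main effect, each of those differences is adjusted with the same slope. The pre-operative score need not predict every post-operative visit equally well. Where the 12-month slope differs from the pooled one, the 12-month contrast is under- or over-corrected for whatever baseline imbalance the trial happens to have, and its standard error is somewhat larger than necessary.

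Non-inferiority is read from one confidence limit for that contrast, with 37 to 42 patients per arm and no stratification described, so a baseline difference of a few points between arms is to be expected by chance. At stake are some precision and the quality of the adjustment at the visit that counts.

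**Working it through.** **1. The design figure.** Inputs from section {14}: margin 11.5, SD 14, "with a power of 90% and using a one-sided type I error rate of 2.5" per cent.

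- n per group = 2 × (1.960 + 1.282)² × 14² / 11.5² = 2 × 10.51 × 196 / 132.25 = 31.1, so 32. The exact t-test version gives 33.
- The stated 37 is not reproduced, but it errs towards more patients. At 37, SE = 14 × √(2/37) = 3.25 and 11.5/3.25 − 1.96 ≈ 1.57, which is about 94% power.
- The dropout step does reproduce: 37/0.9 = 41.1, so 42 per group and 84 in total.

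The mismatch is a separate matter. It is relevant here only because it leaves spare power.

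**2. What a common slope does.** With complete data, the 12-month estimate is the raw 12-month difference minus (common slope × baseline difference). Write d for the common slope minus the 12-month slope and ρ for the correlation of baseline with the 12-month score. Take baseline and outcome SDs both as 14 (the baseline SD is an assumption).

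- Residual variance with the 12-month slope is proportional to 1 − ρ².
- With the common slope it is proportional to (1 − ρ²) + d².
- The error left by a one-SD baseline imbalance is d × 3.25 points at 37 per group.

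| ρ | d | variance ratio | SE increase | power, own slope | power, common slope | error left (points) |
|---|---|---|---|---|---|---|
| 0.3 | 0.1 | 0.92/0.91 = 1.011 | 0.5% | 95.9% | 95.8% | 0.33 |
| 0.3 | 0.2 | 0.95/0.91 = 1.044 | 2.2% | 95.9% | 95.2% | 0.65 |
| 0.3 | 0.3 | 1.00/0.91 = 1.099 | 4.8% | 95.9% | 94.2% | 0.98 |
| 0.5 | 0.1 | 0.76/0.75 = 1.013 | 0.7% | 98.3% | 98.2% | 0.33 |
| 0.5 | 0.2 | 0.79/0.75 = 1.053 | 2.6% | 98.3% | 97.8% | 0.65 |
| 0.5 | 0.3 | 0.84/0.75 = 1.120 | 5.8% | 98.3% | 97.1% | 0.98 |

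In the third row the whole benefit of baseline adjustment is gone (0.91 + 0.09 = 1.00), and power is still 94.2%.

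**3. What d might be.** This was simulated with 37 per group, four assumed post-baseline visits, unstructured covariance and 600 trials per scenario.

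- Slopes falling from 0.6 to 0.3: the pooled slope averages 0.48, so d = 0.18 and the variance ratio is (0.91 + 0.032)/0.91 = 1.04. The model SE is 3.15 against 3.10 with visit-specific slopes, and power is 95.0% against 95.3%.
- Slopes rising from 0.1 to 0.4: the pooled slope averages 0.27, so d = −0.13 and the ratio is (0.84 + 0.017)/0.84 = 1.02. The SE is 3.03 against 3.00, and power is 94.7% against 95.7%.
- The mean estimate was close to zero under both models when the true difference was zero.
- With a true difference at the margin, false non-inferiority was 1.8% against 2.7% (falling) and 3.3% against 2.8% (rising). Simulation error is about 0.6 points, so no inflation is detectable.
- With 12-month dropout depending on the 6-month score and slopes falling, power was 93.8% against 93.7%.

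**4. Other assumptions.** A second set used 40 per arm, baseline SD 18, visit SDs 16, 15, 14 and 14, and serial correlation 0.75. One SD of baseline imbalance is 18 × √(2/40) = 4.0 points.

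- Correlations falling from 0.6 to 0.3, or from 0.6 to 0.2: variance up 3% or 11%, with 0.13 or 0.25 points left per point of imbalance, hence 0.13 × 4.0 = 0.5 or 0.25 × 4.0 = 1.0 points.
- Correlations rising from 0.2 to 0.5, or constant at 0.4: variance ratio 1.00.

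A separate run at 40 per arm gave 3% to 9% for falling correlations, 0% to 2.5% for rising and nothing for constant. Its extreme was 20%, with falling correlations and equal correlation between all visits. At ρ = 0.3, a 20% rise corresponds to about 14 × √(2/40) × √0.91 × √0.20 = 1.3 points for a one-SD imbalance. In no run was the visit-specific slope meaningfully worse.

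**The case against.** The strongest reply is that the sentence in {20a} is shorthand. It omits the main effect of time, which nobody would take to be absent from the model, so the missing baseline-by-time term is weak evidence of what will be fitted. The source is an article, and a separate analysis plan may carry the term. This stands in part: the text does not rule the interaction out. But the article does list the model terms, and as listed they give one slope, so replacing them with a better set is a fair suggestion.

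The second reply is that a single baseline covariate is valid and widely used. That stands. Under randomisation the contrast is unbiased with either model.

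A reader might go further and infer that the 12-month contrast is adjusted with a slope averaged over early recovery. The documents do not support this. Which visits carry PRWE is not visible, and the pooled slope is a covariance-weighted estimate that includes the 12-month visit. Nor does splinting in the first six weeks strengthen the case. If it weakens the link between baseline and early scores, correlations rise towards 12 months, and that is the pattern in which little is lost.

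**Conclusion.** The point holds as a minor improvement to the analysis model. As listed, one pooled baseline slope adjusts the 12-month PRWE contrast. The cost is roughly 0% to 10% extra variance in most scenarios, with 12% in one analytic case and 20% in one extreme simulated case. For a one-SD chance imbalance, up to about 0.5 to 1 PRWE point is left uncorrected (about 1.3 in the extreme case). One point is 9% of the 11.5-point margin (1/11.5).

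All of this depends on assumed correlations, SDs and four assumed visits. With constant slopes the cost is nil.

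A reader might infer that the non-inferiority conclusion is at risk. It is not: there is no systematic bias, no detectable inflation of false non-inferiority, and power stayed above 90% wherever it was calculated.

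**What to change.** In section {20a}, add a baseline-by-time interaction to the mixed model, with time as categorical visit, for PRWE and the other continuous outcomes. State that the primary treatment effect is the 12-month group contrast from that model. If the statistical analysis plan already contains the term, align the published list with it. Settle this before unblinded data are analysed, so that it is not a post hoc modelling choice. The cost is a few degrees of freedom, with no new data and no change to sample size or visits.

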## Discussion

SLAC/SNAC of the wrist is a disabling progressive degenerative condition that is often treated surgically to reduce pain and improve function. Despite the growing number of scientific reports that address the matter, it is still unclear if FCA or PRC provides the most reliable outcome with fewer complications and less overall expenses. The present trial will compare these procedures in a high-quality setting to assist with clinical decision making when treating patients with this type of wrist OA.

PRC and FCA are common procedures for SLAC/SNAC wrist OA. Furthermore, SL-ligament injury and scaphoid non-union may present with irreducible carpal malalignment without significant degenerative changes. This type of condition is resistant to any attempt of reconstruction and will lead to an unfavorable outcome. Arguably, the pathomechanics of pain behind SL dissociation, scaphoid non-union, SLAC, and SNAC I-II wrist are different. Despite these nuances, a wrist surgeon will most likely treat these conditions similarly, namely with FCA or PRC. This trial will recruit patients presenting the different stages of SLAC/SNAC degenerative pattern provided they are not satisfied with non-surgical treatment regardless of the stage of the condition.

FCA was first described by Watson and Ballet in 1984 [2]. Since its introduction, numerous modifications have been described. Most commonly, the number of “corners” fused and implant(s) used will vary between techniques. Kirchner wires are inexpensive, easy to apply, and commonly used even though a rigid fixation cannot be achieved and pin removal is obligatory. Thus, many surgeons prefer more stable internal fixation with an implant(s) that does not necessitate removal (i.e., cannulated compression screws or a locking plate) [34–37].

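### Optional precision gain: the primary PRWE model could also adjust for diagnosis/OA stage, already recorded at baseline; the planned analysis is valid without it

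*Protocol article*

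**What the plan says.** The Protocol article, Statistical methods for primary and secondary outcomes {20a}, plans a mixed model for repeated measurements, "entering group, group*time interaction as fixed factors, study site as a random factor, and baseline value as a covariate to the model". Under Outcomes {12}, "The primary endpoint of the study is PRWE at 1 year after the procedure".

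The trial takes patients by three routes (Table 2, inclusion criterion 1): irreducible carpal collapse after scapholunate (SL) ligament injury with normal cartilage, scaphoid non-union that cannot be reconstructed with normal cartilage, and SLAC/SNAC I-II OA. On these conditions the Discussion says: "Arguably, the pathomechanics of pain behind SL dissociation, scaphoid non-union, SLAC, and SNAC I-II wrist are different". It goes on to say that surgeons would most likely treat them alike, and that recruiting across stages is intended.

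Stage is collected: "Radiological baseline assessment includes wrist OA classification (SLAC/SNAC 0-IV), location of scaphoid non-union" (Outcomes {12}). The consent section {26a} has baseline data collected before randomization. Sequence generation {16a} specifies "permuted block randomization with variable block size" and names no stratification factor.

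**The concern.** PRWE measures pain and disability. The article raises a possible difference in pain mechanism between the conditions it pools, and it records the variable that separates them. It then uses that variable in neither the allocation nor the primary model.

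If diagnosis predicts 1-year PRWE after baseline PRWE is taken into account, two things follow. Some explainable variance stays in the error term, so the interval is a little wider than it need be. And if the arms happen to differ in diagnosis mix, the estimate in that particular trial is shifted by a known mechanism. Adjusting only after such an imbalance has been seen would be open to challenge, so the time to choose the covariate is before unblinding. Non-inferiority depends on where the upper confidence limit falls relative to 11.5 points, so precision has some value here.

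**Working it through.** **Inputs from the article.** Sample size {14} gives "non-inferiority margin 11.5, SD 14", "with a power of 90% and using a one-sided type I error rate of 2.5" per cent, and "the trial will require 37 patients in each group". It recruits 84 patients to allow for 10% loss.

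**Inputs assumed, because the article gives none.** The share of residual PRWE variance explained by diagnosis beyond baseline PRWE (R²) is taken as 0.02 to 0.10. The proportion with normal cartilage is taken as 30%. SD 14 is used as the residual SD of the 1-year comparison; the article does not say whether it is already net of baseline or of diagnosis.

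**1. The plan's own figure.** With a true difference of 0, n per arm = 2 × [14 × (1.960 + 1.282) / 11.5]² = 31.1, so 32, or 33 with the t distribution. The stated 37 is larger, which is conservative and is not part of this point. The step to 84 reproduces: 37 / 0.9 = 41.1, so 42 per arm.

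**2. The planned model without diagnosis.** At 37 per arm, SE = 14 × √(2/37) = 3.25. The 95% half-width is 1.993 × 3.25 = 6.49, so the observed PRC minus FCA difference must be below 11.5 − 6.49 = 5.01 to pass. Noncentral-t power is 93.6%; at 42 per arm it is 96.1%.

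**3. Does leaving diagnosis out inflate the error?** Trials were simulated with 37 per arm, total SD 14 and a binary diagnosis factor with 33% prevalence that was left out of the analysis (40,000 runs per gap). For gaps of 5 and 10 PRWE points between categories, one-sided error at the margin was 0.025 and 0.024, and power was about 0.94. Repeats at 30% prevalence with gaps of 5 to 15 points gave error of 0.024 to 0.026 and power of about 0.94. There is no inflation.

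**4. What adjustment would buy.** Residual SD = 14 × √(1 − R²), at 37 per arm. Two degrees of freedom are spent when R² is above 0; spending one changes power by only about 0.01 percentage points.

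| R² (assumed) | Residual SD | Power | 95% half-width |
|---|---|---|---|
| 0 | 14.0 | 93.6% | 6.49 |
| 0.02 | 13.9 | 94.1% | 6.43 |
| 0.05 | 13.7 | 94.7% | 6.33 |
| 0.10 | 13.3 | 95.7% | 6.16 |

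The gain is therefore about 0.4 to 2 percentage points of power and about 0.1 to 0.3 PRWE points of half-width. To give a sense of scale, R² = p(1 − p)g² / 14². With p = 0.30, an R² of 0.02 to 0.10 corresponds to a gap g of about 4.3 to 9.7 points between categories.

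**5. How often a large imbalance occurs.** With p = 0.30, the SD of the between-arm difference in proportion is √(2 × 0.3 × 0.7 / 37) = 0.107. The chance of a difference of 20 percentage points or more in either direction is about 6% (normal approximation 6.0%, exact binomial 5.6%).

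**The case against.** The strongest case against is that nothing in {20a} is wrong. Site and the baseline value of the outcome make a standard covariate set, and a factor not used in stratification need not be in the model for the analysis to be valid. That stands.

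The prognostic premise is also thin. The only support is one sentence hedged with arguably, followed by the remark that the conditions are treated similarly. A different pain mechanism before surgery is not evidence of a different PRWE a year after it, and baseline PRWE may already carry whatever difference exists. This stands too, and it is why the gain is stated only as conditional on an assumed R².

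A statistical analysis plan that is not shown may already add covariates. That is possible. However, the article lists the model terms explicitly, so this is a comment on a stated choice and not on a missing detail.

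A reader might infer something stronger: that omitting diagnosis biases the primary contrast or lets non-inferiority be declared too easily. The documents do not support this. Take an assumed 10-point gap and an imbalance of exactly 20 percentage points favouring PRC. The shift is 2 points and the within-category SD is √(196 − 0.21 × 100) = 13.2, so the SE of the contrast is 13.2 × √(2/37) = 3.08. The chance of passing at the margin is then about 7 to 8%: (5.01 − 9.5) / 3.08 = −1.46 on the normal scale. Power under the opposite imbalance is about 83%. But these figures apply only within the roughly 3% of trials with so large an imbalance in that one direction. The opposite imbalance lowers the false-pass chance to about 0.3%. Over all randomizations the rates are the 2.5% and 94% found above, and those describe the planned test.

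**Conclusion.** The point holds as an optional, low-cost improvement in precision and not as the correction of an error. The primary model leaves out a baseline factor that is recorded before randomization, is not named as a stratification factor, and might matter for a pain-and-disability score. The planned analysis keeps its one-sided error at about 2.5%, and its power of about 94% at 37 per arm exceeds the planned 90%.

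The benefit of adjusting rests on an assumption that the article does not document, namely that diagnosis predicts 1-year PRWE beyond baseline PRWE. With R² of 0.02 to 0.10 the gain is small against a margin of 11.5 points. Protection against a marked imbalance is a second, modest benefit, needed in about 6% of trials at an assumed 30% prevalence. If the factor is not prognostic, there is no gain.

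**What to change.** Before unblinding, add one binary fixed covariate to the PRWE mixed model: normal cartilage (SL collapse or scaphoid non-union, stage 0) versus SLAC/SNAC I-II OA. Take it from the recorded baseline classification, and confirm that stage 0 there corresponds to the two normal-cartilage entry routes, since the article does not spell out that coding. Keep the model as now written as a sensitivity analysis.

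The cost is one sentence in the analysis plan and one model degree of freedom. No new data, visits or patients are needed.
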